## Abstract

**Background:**

Ethiopia has high rates of maternal and neonatal mortality. In 2019 and 2020, the maternal and newborn mortality rates were estimated at 412 per 1,000,000 births and 30 per 10,000 births, respectively. While mobile health interventions to improve maternal and neonatal health management have shown promising results, there are still insufficient scientific studies to assess the effectiveness of mobile phone messaging–based message framing for maternal and newborn health.

**Objective:**

This research aims to examine the effectiveness of mobile phone messaging–based message framing for improving the use of maternal and newborn health services in the Jimma Zone, Ethiopia.

**Methods:**

A 3-arm cluster-randomized trial design was used to evaluate the effects of mobile phone–based intervention on maternal and newborn health service usage. The trial arms were (1) gain-framed messages (2) loss-framed messages, and (3) usual care. A total of 21 health posts were randomized, and 588 pregnant women who had a gestational age of 16-20 weeks, irrespective of their antenatal care status, were randomly assigned to the trial arms. The intervention consisted of a series of messages dispatched from the date of enrolment until 6-8 months. The control group received existing care without messages. The primary outcomes were maternal health service usage and newborn care practice, while knowledge, attitude, self-efficacy, iron supplementation, and neonatal and maternal morbidity were secondary outcomes. The outcomes will be analyzed using a generalized linear mixed model and the findings will be reported according to the CONSORT-EHEALTH (Consolidated Standards of Reporting Trials of Electronic and Mobile HEalth Applications and onLine TeleHealth) statement for randomized controlled trials.

**Results:**

Recruitment of participants was conducted and the baseline survey was administered in March 2023. The intervention was rolled out from May 2023 till December 2023. The end-line assessment was conducted in February 2024.

**Conclusions:**

This trial was carried out to understand how mobile phone–based messaging can improve maternal and newborn health service usage. It provides evidence for policy guidelines around mobile health strategies to improve maternal and newborn health.

**Trial Registration:**

Pan African Clinical Trials Registry PACTR202201753436676; https://tinyurl.com/ykhnpc49

**International Registered Report Identifier (IRRID):**

DERR1-10.2196/52395

## Background

Ethiopia has one of the highest maternal and neonatal mortality ratios worldwide, with a maternal mortality ratio of 401 per 100,000 live births and a neonatal mortality rate of 33 per 1000 live births [1]. The risk of death due to complications during pregnancy, labor and delivery, and the postnatal period is believed to be reduced with bundles of antenatal care, institutional delivery, and postnatal care (PNC) [2]. However, in Ethiopia, the proportion of women attending at least 4 antenatal visits, delivered at health facilities, and had early PNC service was 43%, 48%, and 35%, respectively [3], indicating there are missed opportunities for almost half of the women who were not able to seek the recommended antenatal visits, institutional delivery, and PNC in the country.

Innovative strategies are required to reduce maternal mortality by improving the use of antenatal care (ANC) services to achieve Sustainable Development Goal 3 by 2030—reducing maternal mortality to fewer than 70 per 100,000 births. Improving child survival also remains a matter of urgent global support. A clear and accessible strategy to achieve this goal is to take advantage of the potential of simple mobile phones to increase the number of ANC visits for prenatal women [4]. Recently, mobile phones have been introduced to disseminate health information and interventions (eg, mobile health [mHealth] interventions) in low- and middle-income countries (LMICs). mHealth is recognized as an important area in implementing global strategies for women’s and children’s health. Although mHealth interventions are promising, there is insufficient scientific research to assess their effects [5]. As of 2022, the number of mobile phone users, including smartphones and feature phones, was 7.26 billion, representing 91.54% of global mobile phone ownership [6]. mHealth has the potential to improve tens of thousands of lives each year. The ubiquity and penetration of mobile phones provide a unique opportunity to leverage mHealth for maternal and newborn care [7]. According to the International Telecommunication Union, mobile phone coverage has increased to 90% of the world’s population and 80% of the rural population [8].

Digital health, or the use of digital technologies for health, has become a prominent field of practice for using routine and innovative forms of information and communications technology to address health needs and improve health knowledge, including in rural areas of LMICs [9,10]. Mobile technology is creating new opportunities to permit safe, accessible, coordinated, and effective maternal and child health care in these regions [11]. Introducing mHealth as a new strategy for health care delivery is seen as a suitable option for reducing the high rates of maternal and child mortality in low-income countries [12,13]. mHealth, a subset of eHealth, is defined as “the use of mobile wireless technologies for health” [9]. SMS is text messaging following mobile network standards. It has been suggested that mobile phone messaging interventions can improve self-management of diabetes, weight loss, physical activity, quitting smoking, and adherence to medication in antiretroviral therapy [14,15]. The use of SMS has also indicated promising outcomes in the promotion of maternal and child health care services [16-20]. However, to date, few studies have evaluated the effect of SMS-based interventions on maternal and newborn health among pregnant and postpartum women in transitioning countries [16,20]. While evidence for SMS-based interventions is well described, the effect of SMS-based message framing intervention for improving maternal and newborn health is limited.

Message framing is the presentation of information in a way that affects the perception, attitude, or behavior of the person receiving it. It is how a message is worded, structured, or framed to impact the target audience’s perception and persuade them to take action [21,22]. There are 2 primary forms of message framing: gain-framing and loss-framing. Gain-framing highlights the advantages or positive results of a decision or action, while loss-framing focuses on the potential negative consequences or losses that could result. The type of framing used depends on the context and objectives of the message, as it can be used to either encourage or discourage specific actions [23,24]. Scholars have been reporting that gain-framed information is more persuasive for disease prevention behaviors as it encourages risk aversion and thus engages in safe disease prevention behaviors. Conversely, loss-framed information is suggested for disease detection behaviors, as it makes people willing to take risks and engage in relatively risky disease detection behaviors [25,26].

The literature on health message framing is extensive and has shown promising effects on health outcomes, including maternal and child health [27,28]. A study by Divdar et al [28] showed significant improvements in oral health knowledge, attitude, intention, efficacy, and practice among the intervention group as compared to the control group, although no significant difference was observed between gain and loss-framed messages. Both gain and loss-framed messages significantly improved breastfeeding self-efficacy in a study conducted in Iran [29]. Another 3-arm intervention has shown significant improvements in complementary feeding knowledge, attitude, self-efficacy, and practice among interventions, with the loss-framed group showing higher improvement than the gain-framed group [30]. However, Frew et al [31] found is no improvement in maternal influenza immunization in their intervention evaluating message framing. These findings indicate inconsistent results regarding which framing method improves maternal and child health care practices [29-31]. Moreover, the evidence on the impact of message framing on maternal and newborn care practice is still unclear in LMICs and needs further assessment [32]. Therefore, to foster our understanding of framing effects and determine which way of information framing has a strong persuasive effect on maternal and newborn health, we need further confirmation.

Although various studies have reported that digital health interventions are effective in improving health service uptake, including maternal and child health services, none, to our knowledge, have considered message framing as a strategy to persuade, change opinions, and encourage the adoption of new behaviors. The main objective of this study is to evaluate the effects of mobile phone messaging-based gain or loss-framed messages on improving maternal health care usage and newborn care practice in the rural Jimma zone.

## Methods

### Setting

The study is being conducted in Manna, Shebe-Sombo, and Dedo districts of Jimma Zone, Oromia, Ethiopia. The districts were selected from 21 districts in the zone after confirming the unavailability of interventions aiming to improve maternal and newborn health services in each of them. Jimma Zone is characterized by weak health infrastructure, high health workers to the population ratio (1:329), only 9 health facilities offering comprehensive emergency obstetric and newborn care and a high maternal mortality ratio (412 per 100,000 live births).

### Study Design

A 3-arm, cluster-randomized trial design with a 1:1 allocation ratio was used.

### Intervention Components

The participants in the intervention were assigned to 3 arms: gain-framed, loss-framed, and control. The detailed description of each arm is presented as follows:

#### Gain-Framed Message

Women in this arm received an automated gain-framed message. The gain-framed SMS text messages, which were tailored based on individual women’s gestational age (GA), expected delivery time, and postnatal period, were sent from the time of enrolment during ANC until the end of the postnatal period to the established list of participants’ phone numbers. Women in this group also received the existing maternal care provided at the health facility.

#### Loss-Framed Messages

Women in this arm received automated, loss-framed messages. The loss-framed SMS text messages, which were tailored based on individual women’s GA, expected delivery time, and postnatal period, were sent from the time of enrolment during ANC until the end of the postnatal period to the established list of participants’ phone numbers. Women in this group also received the existing maternal care provided at the health facilities.

#### Control Group

Participants in the control group received existing ANC and PNC services provided at health facilities. According to the recent ANC guidelines, pregnant mothers are expected to have 8 ANC and 3 PNC contacts. In addition to these cares, counseling services is recommended on the following topics during ANC visits: (1) lifestyle modification, (2) danger signs and symptoms, (3) birth preparedness and complication readiness, and (4) other issues such as family planning, cord care, bathing, breastfeeding, child immunization, and screening for cervical cancer [33].

### Intervention Packages

The intervention messages and the messaging system, which automatically dispatches these messages, were developed. These messages were developed based on the concept of message framing, with half of them developed in the form of a gain frame—emphasizing the benefits of maternal and newborn health care practices (eg, choosing to put your new baby to the breast in the first hour he or she is born will increase a baby’s protection from many diseases and illnesses). The other half of the messages were developed as a loss frame—emphasizing loss as a result of not using maternal health services and practicing newborn care (eg, failing to put your new baby to the breast in the first hour he or she is born will lower a baby’s protection from many diseases and illnesses). Multimedia Appendix 1 provides more examples of both gain- and loss-framed messages.

The content of the messages was evaluated by mothers and experts before it was used in the intervention. Initially, 120 (60 for each form) English version messages were drafted within the character count of 160, based on the Ethiopian Ministry of Health’s guidelines and the World Health Organization’s recommendations. After discussing with the research team, 32 (16 from each form) messages were discarded. The remaining 88 messages were translated into the Afan Oromo language and used for content evaluation. Mothers evaluated the content of these 88 messages through a card sorting activity, and 10 messages (5 from each form) that were not well understood by mothers were discarded. Following the card sorting activity, 8 experts evaluated the retained 78 messages (39 for each form) using 10 statements. The experts suggested modifications for 14 messages (13 loss-framed and 1 gain-framed), and all of these messages were modified and refined based on the suggestions.

Finally, 39 messages for each message form were retained under 10 thematic areas: nutrition, lifestyle modification, danger signs, birth preparedness, complication readiness, breastfeeding practice, labor, newborn care, immunization, and antenatal and PNC usage. These messages were dispatched using locally developed software that manages the schedule and sends the messages automatically. To facilitate this, a domain, layer 3 VPN, and short code were purchased from Ethio-telecom Company. The software program includes an interface to enter the participant’s name, gestational week, mobile phone number, message type, message category, language option, report generation, and feedback options.

### Eligibility Criteria for Clusters and Participants

Clusters (Kebeles) with good mobile network coverage in 3 of the selected districts were eligible for randomization. Pregnant women with a GA of 16-20 weeks who either owned a mobile phone themselves or had a family member who owned one, lived in the selected cluster for at least 6 months, provided consent to participate in the intervention, and shared their phone number were eligible for the trial. Pregnant mothers who were unable to read mobile phone messages and had plans to relocate from the study cluster during the follow-up period were excluded from the intervention.

### Sample Size Determination

#### Sample Size for the ANC Visit

The method suggested by Hooper et al [34] for cluster randomized trials with repeated cross-sections was used for the calculations. This method requires calculating 2 design effects, which are then used to inflate the sample size for individual randomization to account for the within-period intracluster correlation coefficient (ICC) and the between-period ICC. A sequence of steps has been followed to get the final sample size for the current 3-arm cluster randomized trials with repeated cross-sections. For ANC, we first calculated the individual randomization trial using the following assumptions: P1—the proportion of women attending ANC for more than 4 visits among the control group 23.27% [35], power=80%, 2-sided α=0.025, effect size=15%, and Zα/2 adjusted for multiple comparisons using a Bonferroni correction of 2.24. Individual randomization sample size (n) is calculated as follows:

Next, the design effect (*d*_c_) due to cluster randomization was calculated as *d_c_* = 1 + (*m* – 1)*ρ*. Here, the following parameters were considered: the within-period ICC(*p*) was assumed to be 0.003 [36], and the cluster size (m) was assumed to be 28. The calculation yielded a design effect due to cluster randomization *dc* = 1 + (*m* – 1)*ρ* = 1.08. Additionally, the design effect due to repeated assessment was calculated as *d*_r_=(1–*r*^2^), where *r* is the correlation between samples from the same cluster at different times and determined as 
[figure not shown]
. Based on this, *d*_r_ was calculated using assumptions: within-period ICC=0.003, autocorrelation coefficient (π) of 0.8 (to allow for a 20% decay of the correlation from within to between different periods) [37], and *m*=28 and 
[figure not shown]
=0.062. Thus, the design effect due to repeated assessment was *d*_r_=(1–*r*^2^)=0.996.

To arrive at the final sample size per arm, the sample size for individual randomization is multiplied by both design effects, resulting in (n×*d*_c_×*d*_r_)=188. Considering a 4% loss to follow-up, the final sample size for each arm is 196 and this gives a total sample size of 588 when ANC was used as the primary outcome of the intervention.

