#### Sample Size for Newborn Practice

For newborn care practice, the same procedure described earlier was used. First, the individual randomization sample size was calculated to be 118 based on the following assumptions: P1—the proportion of exclusive breast feeding among the control group of 74.8% [38], power=80%, 2-sided α of 0.025, effect size=15%, and *Z*α/2 adjusted for multiple comparisons using a Bonferroni correction=2.24. Then, the design effect (*d*_c_) due to cluster randomization was calculated as *d_c_* = 1 + (*m* – 1)*ρ* = 1.35 by considering the following parameters: within-period *p* of 0.013 [39] and cluster size assumed to be 28. The design effect due to repeated assessment was calculated as *d*_r_=(1–*r*^2^)=0.953, where the correlation between samples from the same cluster at different times *r*=0.251 by using assumptions: within-period ICC=0.013 [39], autocorrelation coefficient (π) of 0.8 (to allow for a 20% decay of the correlation from within to between different periods) [37], and *m*=28. By inflating the sample size under individual randomization with the 2 design effects as (n×*d*_c_×*d*_r_)=152. Considering a 4% loss to follow-up, the total sample size was 475.

Therefore, the sample calculated for ANC was larger (588) and was the final sample size of the trial to arrive at 21 clusters (7 per arm) and an average of 28 eligible pregnant mothers.

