
### Data Collection Procedures and Tools

The baseline survey was conducted in March 2023, while the end-line survey was conducted in February, 2024. Trained interviewers collected data for both the baseline and end-line surveys through face-to-face interviews using a structured questionnaire. The questionnaire addressed various domains, including sociodemographic factors, socioeconomic factors, obstetric history, maternal health service usage, newborn care practice, knowledge about maternal health services, knowledge about maternal danger signs, knowledge about newborn danger signs, knowledge about newborn care practices, attitude toward maternal health services, attitude toward newborn care practice, self-efficacy toward maternal health services, self-efficacy toward newborn care practice, iron supplementation, and maternal and neonatal morbidity. Participants who were lost to follow-up were recorded, along with their reasons for discontinuation and the outcome of their pregnancy. The data were checked for inconsistencies and errors during the data collection period by dedicated supervisors and submitted to the central data management unit.

A total of 10 data collectors and 2 supervisors were recruited during each data collection period. A 2-day training was given for data collectors and supervisors on the questionnaire content, measurements, ethical issues, and how to use the ODK app (during end-line assessment), and they were kept uninformed about cluster allocation.

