### Data Analysis Plan

Double-data entry was accomplished using Epi-data (version 4.6, released in 2020; the EpiData Association) and exported to the SPSS (version 25; IBM Corp) for analysis. The report of this study will be made according to the CONSORT-EHEALTH (Consolidated Standards of Reporting Trials of Electronic and Mobile HEalth Applications and onLine TeleHealth) standards for reporting randomized controlled trials. Exploratory subgroup analysis was done to identify whether the effects of intervention vary with sociodemographic characteristics, socioeconomic characteristics, obstetric history, and psychological factors. To assess the characteristics of the study population through the lenses of different variables, selected data were tabulated by study arms; this helped us to identify variations and similarities among study arms. The summary statistics used for categorical variables were frequencies and percentages. For continuous variables, the mean and standard deviation will be presented.

To observe the effectiveness of mobile phone messaging-based message framing interventions for improving maternal and newborn health service usage, we will use an intention-to-treat approach where all randomized participants will be included in the statistical analysis, regardless of whether they received the intervention or not. A generalized linear mixed model will be used to adjust for both the clustering effect and the participant-level intracluster correction. The outcome variables are assumed to have a multivariable normal distribution. The odds ratio will be used to measure the effectiveness of the intervention on the outcome variable with a 95% CI.

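### The sample size takes a repeated cross-sections reduction (d_r) that has no documented basis in a single cohort with end-line primary outcomes, and the printed newborn r of 0.251 contradicts its own inputs

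*Protocol article*

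**What the plan says.** In the protocol article, Sample Size for the ANC Visit states that a method "for cluster randomized trials with repeated cross-sections was used for the calculations", and describes its result as the "final sample size for the current 3-arm cluster randomized trials with repeated cross-sections". An individually randomized sample size is multiplied by a clustering design effect, d_c = 1 + (m − 1)ρ, and by a factor for repeated assessment, d_r = 1 − r². Here r is the correlation between samples taken from the same cluster at different times. The ANC calculation prints r = 0.062 and d_r = 0.996, then 188 per arm, 196 after 4% loss, and 588 in total. Sample Size for Newborn Practice repeats the steps with the correlation "at different times *r*=0.251 by using assumptions" that include an ICC of 0.013, and prints d_r = 0.953, 152 per arm and 475 in total. The larger figure, 588, is adopted.

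Other sections describe one group of women. Recruitment selects 28 eligible women per kebele and records name, phone number and gestational age. The message sections tie the texts to each woman's own gestation, expected delivery and postnatal period. Under Data Collection Procedures and Tools, "Participants who were lost to follow-up were recorded, along with their reasons for discontinuation and the outcome of their pregnancy". Operational Definitions makes maternal health service usage depend on at least 8 ANC visits, a facility birth and postnatal contact within 7 days. It defines newborn care from birth to 28 days.

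The Data Analysis Plan proposes a generalized linear mixed model to "adjust for both the clustering effect and the participant-level intracluster correction".

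**The concern.** The factor d_r lowers the required number because information on the outcome from an earlier period in the same clusters is used in the comparison. That needs an earlier measurement of the outcome and an analysis that uses it. A woman at 16-20 weeks has not delivered, has had no postnatal contact and has not cared for this newborn, so no baseline value of either primary outcome exists for the index pregnancy. If nothing earns the reduction, both stated requirements are too small.

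The printed newborn r also looks inconsistent with the d_r printed in the same sentence, so a reader cannot tell which figure was used.

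The model sentence mentions a participant-level adjustment without saying which outcomes it covers. For a binary outcome observed once per woman, a participant random effect cannot be separately estimated.

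**Working it through.** **Inputs (the two sample-size sections).** z for α = 2.24, as "adjusted for multiple comparisons using a Bonferroni correction of 2.24"; z for 80% power = 0.84; difference 15 percentage points; m = 28; autocorrelation π = 0.8; loss 4%. ANC: control proportion 0.2327, ρ = 0.003. Newborn: control proportion 0.748, ρ = 0.013.

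**Formulas.**
- n = (2.24 + 0.84)² [p1(1 − p1) + p2(1 − p2)] / (p1 − p2)². The ANC formula is not legible in the text. This unpooled form is assumed because it gives the printed newborn 118 and the printed ANC end result.
- r = mρπ / [1 + (m − 1)ρ]. This formula is also a missing figure. The standard form is assumed because it gives the printed ANC r.

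**Reproducing the plan.**

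| | ANC | Newborn |
|---|---|---|
| n | 9.4864 × 0.41479 / 0.0225 = 174.9 | 9.4864 × 0.28009 / 0.0225 = 118.1 |
| d_c | 1 + 27 × 0.003 = 1.081 | 1 + 27 × 0.013 = 1.351 |
| r | 0.0672 / 1.081 = 0.0622 (printed 0.062) | 0.2912 / 1.351 = 0.2155 (printed 0.251) |
| d_r | 0.9961 (printed 0.996) | 0.9535 (printed 0.953) |
| n × d_c × d_r | 188.3 (printed 188) | 152.1 (printed 152) |
| after 4% loss | 188 / 0.96 = 195.8, so 196; × 3 = 588 | 152 / 0.96 × 3 = 475 |

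Every printed figure is recovered except the newborn r.

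**The printed r.** This check does not depend on the missing formula: 1 − 0.251² = 0.937, not 0.953. Carried forward, 118 × 1.351 × 0.937 = 149.4 per arm, and 149.4 / 0.96 × 3 = 467. The article prints 152 and 475, so those came from r ≈ 0.2155. The printed value looks like 0.215 with two digits swapped.

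**Without the reduction (d_r = 1).**
- ANC: 174.9 × 1.081 = 189.05; / 0.96 = 196.9, so 197 per arm and 591 in total. Rounding 189.05 up to 190 first gives 198 per arm and 594.
- Newborn: 118 × 1.351 = 159.4; / 0.96 = 166.1 per arm, so 498 in total, or 501 with 167 per arm.

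**Power at 188 analysed per arm, d_r = 1, same unpooled formula.**
- ANC: effective n = 188 / 1.081 = 173.9; √(173.9 × 0.0225 / 0.41479) − 2.24 = 0.831, which is about 79.7%.
- Newborn: effective n = 188 / 1.351 = 139.2; √(139.2 × 0.0225 / 0.28009) − 2.24 = 1.10, which is about 86%.

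Under a pooled-variance formula, ANC power is 79.0% with d_r and 78.8% without. The loss is a fraction of a percentage point under either formula.

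**The case against.** The strongest reply is that r is a cluster-level correlation and needs neither the same women nor the same pregnancy. The questionnaire domains listed under Data Collection Procedures and Tools include maternal health service usage, newborn care practice and obstetric history, so baseline answers might concern an earlier birth in the same kebele. This stands as a possibility, and it is why the finding is that the reduction is undocumented rather than impossible in principle. The article never says that an earlier birth supplies the baseline. Eligibility does not require a previous birth, so first-time mothers would have no value, although d_r is computed with m = 28. The analysis as described also has no term that would use such a baseline.

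A reader might infer that the planned model itself treats the data as repeated cross-sections or fits a baseline-by-time contrast. The Data Analysis Plan says neither. A participant-level adjustment points, if anything, to repeated measures on the same women. A reader might also infer that a participant random effect is planned for the once-measured primary outcomes. The sentence covers all outcomes, and knowledge, attitude and self-efficacy scores are domains of both surveys, where such a term is legitimate. The wording is loose, but it does not show a primary model that cannot be estimated.

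It is also fair to say that the r error has no consequence downstream, and that 475 is not the operative sample size. Both are accepted.

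**Conclusion.** The point holds in limited form. The sample-size text names a design that the rest of the article does not describe, and takes a precision credit for which no baseline outcome or analysis term is documented. It also prints an r that disagrees with its own inputs and with the next printed figure.

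The size is minor. The newborn requirement rises from 475 to about 500 (about 5%) and remains covered by 588. The ANC requirement rises from 588 to about 591, or 594 with stricter rounding, and ANC power at 588 is about 79.7%. A reader might infer that the trial is underpowered because of this. The figures do not support that: the shortfall is of rounding size.

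These results assume the unpooled formula and the standard form for r, each supported by the printed figures it returns. They also take the article's control proportions, ICCs, 15-point difference and 4% loss as given. Reading the trial as a single cohort rests on the recruitment, messaging and loss-to-follow-up text; no section describes a separate end-line sample.

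**What to change.** - Describe the design as a cohort randomized by cluster, with primary outcomes measured at end-line, and remove the repeated cross-sections label.
- Set d_r = 1 in both calculations. Restate the newborn total as about 500 and the ANC requirement as about 591, and note that 588 gives about 79.7% power for ANC.
- If the formula for r is kept anywhere, print the newborn value as 0.216.
- In the Data Analysis Plan, specify a kebele random intercept for the once-measured primary outcomes, and limit any participant-level term to outcomes measured at both surveys.
- If answers about an earlier birth were meant to serve as the baseline, say so, state how first-time mothers are handled, and name the model term that uses those answers. Only then could a d_r below 1 be justified.

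The cost is restated figures and a few sentences of model wording. Recruitment is unaffected. The article reports the analysis as still to be completed, so by its own timeline the model wording could be settled first.
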